### Patient and public involvement

The Dutch society for colorectal cancer patients (Stichting Darmkanker) were involved in the creation and wording of the patient information folder. Functional and quality of life outcomes in this study are based on comments from patients, an area not often researched after LLND surgery.

### Data management

Data will be prospectively collected and stored in a Castor EDC database (Castor Electronic Data Capture, 2019, online, available at: https://castoredc.com) managed by the central researchers. Specialists in the participating local centres will record data for their included patients. During data entry, they will be able to view other data regarding patients from their own institute, enabling correlation between, for example, radiology slides and radiation fields. Specialists from one centre cannot access the data of patients from other centres.

### Sample size

The sample size is based on a historical control group with an average 3-year LLR rate of 13% (11% Snapshot and 16% Consortium) in low LARC with LLNs ≥7.0 mm after (C)RT+TME (without LLND), which is the current standard treatment in Europe.^5 6 14^ It is hypothesised that (C)RT+TME+LLND can reduce this rate to 6%, as found by the Consortium study. A one-group χ^2^ test with a 5% two-sided significance level will have 90% power to detect the difference between the null hypothesis proportion of 0.13 and the alternative proportion of 0.06 when the sample size is 190. If correcting for a drop-out rate of 5%, 200 patients are needed. Included patients in need of more extensive surgery (ie, pelvic exenteration or presumed inability to spare the hypogastric nerves on MRI) will be registered and analysed as a separate cohort since these more extensive tumours have higher LLR rates and cannot undergo nerve-sparing LLND.

Annually, approximately 882 patients present with low LARC and are treated with neoadjuvant therapy in the Netherlands.^14^ Considering 122 (14%) of these patients have LLNs ≥7.0 mm, a minimum 2.5-year inclusion period is needed to achieve the estimated sample size (expecting 60% of eligible patients to be enrolled).^14^ As some of the eligible patients will undergo open surgery, it is expected that the inclusion period may require an extension. An interim analysis will be carried out after the inclusion of the first 75 participants. The goal of this interim analysis is to evaluate early indicators of effectiveness concerning oncological outcomes, particularly LLR rate, and to evaluate safety by examining short-term surgical complications (within 90 days) and early functional outcomes (urogenital dysfunction within 3 months). The results will help improve the preoperative information provided to patients. If the interim analysis reveals a high LLR rate that suggests that the hypothesis may not be achievable or significant morbidity within 3 months of surgery, the study team will consider to prompt the study ahead of time.

Additionally, patients with rectal cancer and an LLN of 5.0–6.9 mm SA with at least one malignant feature will be investigated. For this analysis, a sample size calculation is impossible due to limited data. Therefore, all eligible patients in this group will be collected during the study period.

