### Study design

The LaNoReC study is an international multicentre prospective registration study endorsed by the Dutch Colorectal Cancer Group. This study started in 2021 but was temporarily paused due to a major protocol revision. The initial protocol imposed a specific treatment (C(RT) without a boost, restaging MRI and LLND), which would have a major impact on accrual. Therefore, the protocol evolved towards the current prospective registration study, as demonstrated in figure 1. Approximately 38 Dutch hospitals, in which the multidisciplinary team has sufficed the training demands, will be open to include patients. International centres can join after following similar training sessions as the Dutch clinicians, which are organised by the LaNoReC study team. All included patients will undergo optimised standard of care, including MRI assessment by a trained radiologist, neoadjuvant radiotherapy delineation by a trained radiation oncologist, nerve-sparing LLND by a trained surgeon and evaluation of the resection specimen by a trained pathologist or grossing assistant. The study is registered at clinicaltrial.gov: NCT04486131.

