### Nerve-sparing LLND procedure by trained surgeons

LLNDs will only be performed by a select team of surgeons after completing adequate human cadaver training, intensive proctoring and assessment of procedural videos. Only surgeons who participated in this training can be nominated with their hospital to act as referral centre or the surgeons can be invited to perform the resection in the (local) referring centre. All ‘study-LLND’ procedure videos will be discussed during monthly meetings for quality control.

Patients with primarily enlarged (≥7.0 mm SA) LLNs are advised to undergo an LLND. Moreover, LLND should be considered in patients with an intermediate (5.0–6.9 mm SA) LLN with at least one malignant feature. LLNDs should be performed according to a minimally-invasive, nerve-sparing technique. If preoperative MRI shows the lateral extension of the tumour into the nerve plexus or an exenteration is required, the patient will still be included to analyse oncological and functional outcomes; however, the patient is not included in the main analyses (see sample size section). If in a shared decision-making process, the patients decide not to undergo an LLND, they remain in the study and are followed for collection of oncological outcomes. In case of a complete clinical response of the tumour and shrinkage of the LLN(s), a patient may enter a watch-and-wait protocol; in these cases, patients should be closely monitored and an LLND may be omitted.

The surgical technique for LLNS has been previously described in detail.^24^ The procedure involves the excision of all lateral lymphatic tissues within the internal iliac and obturator compartment along three anatomical planes: (1) the medial plane defined by the ureter and pelvic plexus (ureterohypogastric fascia), (2) the lateral plane bounded by the psoas and internal obturator muscle and (3) the dorsal plane defined by the internal iliac vessels and the sciatic nerve. It is important to note that the lymphatic tissue along the external iliac arteria is not dissected during this procedure.

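### The stated 90% power holds only if nearly all analysed patients undergo LLND, or if the mixed population still reaches 6%; the protocol makes LLND optional and does not allow for this

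*Protocol article*

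**What the plan says.** Sample size section (Protocol article). The null rate is a historical "average 3-year LLR rate of 13% (11% Snapshot and 16% Consortium") for radiotherapy-based treatment plus TME without LLND. The alternative is tied to a different treatment: "It is hypothesised that (C)RT+TME+LLND can reduce this rate to 6%, as found by the Consortium study". The calculation follows: "A one-group χ^2^ test with a 5% two-sided significance level will have 90% power" for the "null hypothesis proportion of 0.13 and the alternative proportion of 0.06 when the sample size is 190". The only allowance is for loss: "If correcting for a drop-out rate of 5%, 200 patients are needed".

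Section on the nerve-sparing LLND procedure. "Patients with primarily enlarged (≥7.0 mm SA) LLNs are advised to undergo an LLND". If, after shared decision-making, "the patients decide not to undergo an LLND, they remain in the study and are followed for collection of oncological outcomes". The same section lets LLND be left out for complete responders who enter watch-and-wait. Patients with nerve-plexus extension or a need for exenteration are expressly kept out of the main analyses, and the Sample size section puts them in a separate cohort. No such exclusion is stated for decliners or watch-and-wait patients.

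Study design section. "All included patients will undergo optimised standard of care"; the list that completes this sentence names nerve-sparing LLND as one of the elements.

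**The concern.** The alternative of 6% describes patients who all had LLND, whereas the enrolled population may include patients who did not. On the protocol's own figures, enlarged-node patients treated without LLND have an LLR rate of about 13%, which is the null value. Each such patient in the primary test moves the expected rate from 6% towards 13% and so lowers power. A decliner who completes follow-up is not a drop-out, so the step from 190 to 200 does not help.

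The comparison is single-arm against a fixed 13%. If the test misses, nothing in the stated design separates optimised care that did not work from LLND that was not done often enough. The miss could then be read as failure of the strategy.

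**Working it through.** **Inputs.** From the Sample size section: p0 = 0.13, p1 = 0.06, two-sided alpha 0.05, power 0.90, n = 190, drop-out 5%, and source rates without LLND of 11% and 16%. Assumed, because the protocol does not give them: f, the share of analysed patients without LLND, and q, their 3-year LLR rate.

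**Step 1: reproduce the plan.** One-sample test of a proportion, normal approximation:

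n = [1.960·√(p0(1−p0)) + 1.282·√(p1(1−p1))]² / (p0−p1)²

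= [1.960·0.3363 + 1.282·0.2375]² / 0.07² = 189.45, rounded up to 190. Then 190/0.95 = 200.

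Power at n = 190 is Φ{[(p0−p1)·√n − 1.960·√(p0(1−p0))] / √(p1(1−p1))} = Φ(1.287) = 90.1%. The exact binomial power of the same test (reject at 15 or fewer LLRs) is 89.1%. The plan's figures reproduce.

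**Step 2: patients without LLND are analysed.** The expected rate is p = (1−f)·0.06 + f·q, which replaces p1 in the power formula with n kept at 190. Example with f = 0.10 and q = 0.13: p = 0.9·0.06 + 0.1·0.13 = 0.067, and power = Φ(0.837) = 79.9%.

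| f | q = 11%: rate, power | q = 13%: rate, power | q = 16%: rate, power |
|---|---|---|---|
| 0% | 6.00%, 90.1% | 6.00%, 90.1% | 6.00%, 90.1% |
| 5% | 6.25%, 86.9% | 6.35%, 85.4% | 6.50%, 83.2% |
| 10% | 6.50%, 83.2% | 6.70%, 79.9% | 7.00%, 74.5% |
| 20% | 7.00%, 74.5% | 7.40%, 66.7% | 8.00%, 54.4% |
| 30% | 7.50%, 64.6% | 8.10%, 52.4% | 9.00%, 35.3% |

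Exact binomial powers for q = 13% are close: 79.4% at f = 10%, 66.7% at 20%, 52.7% at 30%. With q = 13%, power reaches 88% at f of about 2.4% and 80% at about 9.9%.

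**Step 3: patients without LLND are left out and not replaced.** The rate stays at 6% but n shrinks: 190·0.95 ≈ 180 gives 88.1%, 190·0.90 = 171 gives 86.0%, 190·0.80 = 152 gives 80.5%.

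**Step 4: when there is no loss.** If q = 6%, the mixed rate is 6% and power stays at 90.1% for any f. It also stays there if LLND recipients do better than 6%. With q = 13%, recipients would need (0.06 − 0.1·0.13)/0.9 = 5.2% at f = 10%, or (0.06 − 0.2·0.13)/0.8 = 4.25% at f = 20%.

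**The case against.** The strongest reply is that the power statement is correct as written: at a true rate of 6% and n = 190, power is 90%. A reader might infer from the optional LLND that the design simply lacks 90% power, or has it only if every patient undergoes LLND. The protocol supports neither. It gives no uptake and no LLR rate for patients without LLND under optimised care, and 90% holds whenever the analysed population's rate is 6%, whatever the mix. This part of the reply stands.

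It can also be said that staying in the study is not the same as counting in the primary test, since the exenteration and plexus cases are followed too and yet are kept out of the main analyses. The hypothesis names the LLND regimen, and the remark that open surgery may lengthen accrual could mean that only patients who have the study procedure count towards the target. So the inclusion of decliners is not stated, and this part stands as well. But it remains the better reading: the exclusion is written for one group, and the sentence on decliners follows at once without it. The primary objective concerns enlarged-node patients under optimised care, not LLND recipients only. If the other reading is right and the patients left out are not replaced, power still falls (Step 3); full replacement through longer accrual would avoid that, but is not stated for these patients.

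Finally, 13% may be too high for patients without LLND. Watch-and-wait patients are selected complete responders, and the Discussion says the Snapshot restaging results do not apply to them. For decliners the protocol argues the other way: its Introduction reports considerable LLR risk despite adequate radiotherapy coverage and concludes that further reduction may need LLND. The range of q in Step 2 is the fair answer to this uncertainty.

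**Conclusion.** The concern holds in conditional form. The 90% power requires either near-complete LLND uptake among the analysed patients or a mixed population that still reaches 6%. The protocol secures neither and does not state the dependence. With 10% to 20% of the 190 lacking LLND, power lies between 83.2% and 54.4% over the protocol's own historical rates without LLND (79.9% to 66.7% at its average of 13%), or between 86.0% and 80.5% if these patients are dropped without replacement. The figures assume exactly 6% in LLND recipients. Both the share without LLND and the use of historical rates for those patients are assumptions, not facts from the protocol. Separately, the Study design section describes care that includes LLND for all included patients, which does not agree with the section on the LLND procedure.

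**What to change.** 1. State that the primary analysis covers all enlarged-node patients managed under the optimised strategy, except the separate extensive-surgery cohort. This fits the primary objective. Say explicitly how decliners and watch-and-wait patients count, including the time origin for a patient who has no operation, since the endpoint is timed from surgery.
2. Replace the single 90% figure with a short table of power by assumed LLND uptake and by LLR rate without LLND, as in Step 2, and state the uptake the investigators expect.
3. Add a supportive analysis in LLND recipients, read with caution because recipients are a selected group.
4. Reconcile the Study design section with the LLND procedure and Sample size sections.

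The cost is a less favourable power statement and one extra analysis; no extra patients are needed. Restating power does not restore it. For scale, keeping 90% with q = 13% would take 242 evaluable patients (242/0.95, so 255 in total) at 10% without LLND, or 316 (333 in total) at 20%. Whether to enlarge the study is for the sponsor to decide once an uptake assumption is on record.

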### Ethics and dissemination

The medical ethics board of the VU Medical Centre, the Netherlands, centrally approved the study on 23 November 2022 (reference 2021.0524). All participating centres need to obtain local approval of the study protocol and all patients will provide written informed consent before participation. Results obtained from the data collected in this study will be published in peer-reviewed medical journals.

## Discussion

The LaNoReC study is the first study that will evaluate oncological and functional outcomes of optimal standardised care for rectal cancer patients with enlarged LLNs after dedicated training of the whole multidisciplinary team. An earlier study showed that this training leads to significant improvement in reporting by radiologists,^27^ consistent delineation by radiation oncologists, nerve-sparing minimally invasive LLND by surgeons and assessment of the pathological specimen with attention for LLNs. Considering the high risk of LLR for those with enlarged LLNs when treated with neoadjuvant therapy and TME alone, the LaNoReC study will evaluate whether these refined treatment strategies including adequate radiotherapy and LLND surgery will result in a reduction of 3-year LLR rate from 13% to 6%, corresponding to 15 adequately treated patients to prevent one LLR.

The proposed study design is a prospective registration study with detailed data collection and outcome analysis, in which training has been applied to the various aspects of the diagnostic process and subsequent treatment. This study design, rather than a randomised controlled trial, was chosen because an earlier attempt in 2016 by Wei *et al* to investigate the additional value of LLND after neoadjuvant CRT in a randomised setting was terminated early due to low enrolment.^28^ Moreover, it would be hard to define a control group, because current practice comprises very heterogeneous treatment strategies. In addition, it was chosen not to impose actions (such as mandatory CRT without a boost), because due to new evidence and training of the multidisciplinary team in participating centres, the control intervention does not exist anymore. This might be overcome by cluster randomised trials, but there is a high risk of adapting routine practice towards the study intervention. Moreover, there is a lack of equipoise considering the optimised treatment versus routine practice, and one might even state that it is unethical to withhold patients the most optimal treatment. As a result, the prospective registration nature of this study was found to be most appropriate.

The inclusion criteria for the LaNoReC study are based on the Snapshot and the Consortium study, in which the combination of (C)RT and TME was insufficient for adequate treatment of patients with enlarged LLNs.^5 14^ Besides short-axis size, the recurrence rates seem to be also influenced by other radiological criteria, such as the presence of malignant features which increased the LLR rate in intermediate LLNs to 8% (vs 2% in absence of malignant features). In enlarged nodes, the presence of two or more malignant features was associated with an increased LLR rate of 17% after 4 years, while no LLR developed if such features were absent. Since the influence of malignant features has only been described in small subgroups and should be interpreted with caution, the inclusion criteria and LLND recommendations for the LaNoReC study are based on short-axis size only for enlarged nodes and intermediate nodes specifically combined with the presence of malignant features. By including this intermediate node group, the LaNoReC study aims to dissolve the current lack of knowledge regarding treatment options and oncological outcomes in those patients. After thorough evaluation during multidisciplinary meetings and a shared decision-making process with the patient, an LLND can be considered to lower the LLR rate.

The inclusion criteria described in the previous paragraph should be based on primary MRI, as the Consortium study is the only study which found that sufficient downstaging on restaging MRI (shrinkage of iliac and obturator LLNs to ≤4 mm and ≤6 mm, respectively) could avoid LLND.^5^ The Snapshot study, however, showed that downsizing of LLNs below the Consortium cut-offs still resulted in an unacceptably high LLR rate of up to 15%.^14^ The inclusion criteria for the LaNoReC study are based on the results of the Snapshot study because of the high validity of these findings due to the training of radiologists. Exempted from this are those with a complete clinical response for which a watch-and-wait trajectory is increasingly applied. Although these patients were not included in the Snapshot study, and therefore restaging results are not applicable to this group, we believe an LLND can be omitted in these cases and close surveillance is justified.

In this study, patients can be treated with different neoadjuvant schedules, provided it contains radiotherapy. This allows the multidisciplinary team to choose a treatment strategy based on tumour features, such as extramural venous invasion or tumour deposits. Although an increased LR rate for patients treated with the RAPIDO schedule has been reported, these patients will still be included together with the other neoadjuvant schemes to increase external validity and optimal accrual of the study, thereby avoiding allocation bias related to disease characteristics that will guide decision-making.^26 29^

There are numerous strengths to this study. First, the Dutch participating centres have participated in validated training sessions by experts from the LaNoReC study team, these training sessions will be organised again for interested international centres, which are only allowed to join when the whole multidisciplinary team has sufficed the training criteria. Working internationally increases the external validity of the study and allows for a wide range of eligible patients to be included. Most importantly, this study depends on and strengthens multidisciplinary collaboration and allows for the direct implementation of accurate diagnostics and treatment. This teamwork will increase awareness in all involved specialties and encourage active communication regarding LLNs during multidisciplinary meetings, which will increase individual accuracy during diagnostics and treatment.

Currently, there is no other prospective study investigating the outcomes of LLND in patients with enlarged LLNs. Therefore, the LaNoReC study will provide new and insightful information regarding this newly developed treatment strategy. While a decrease in LLR is essential for the accordance and universal establishment of multidisciplinary treatment, quality of life and morbidity outcomes will also provide novel insights into this treatment in Western patients.

## Data Availability

Data are available upon reasonable request.
